## Flow Chart

Screening

(all patients admitted to hospital, inclusion and exclusion criteria)

Patient information and

(written) informed consent

Study inclusion and baseline examination

Randomisation to either group art therapy (AT) or treatment as usual (TAU)

(via central pharmacy of the Charité University Medicine Berlin)

Intervention period (6 weeks)

(2 AT sessions of 90 minutes per week vs. TAU)

Post-treatment examination (at week 6)

Follow-up examination (at week 12)

# Introduction

## Introduction and Background Information

Schizophrenia is a serious mental disorder affecting up to 1% of individuals worldwide [7]. Despite considerable advances of treatment options, particularly regarding antipsychotic pharmacotherapy, about two thirds of patients develop a longstanding or recurrent course of the disease and have to face severe consequences with respect to their quality of life, vocational and social exclusion as well as multiple hospitalisations. A considerable share of patients experience permanent or recurrent symtoms like delusions and hallucinations or suffer from negative symptoms that limit their motivation and drive as well as hedonic experience. Beside pharmacological antipsychotic treatment, which is often linked to substantial risks and side-effects, psychotherapeutic approaches to schizophrenia have been increasingly given consideration in recent decades [8]. As a result, a substantial body of scientific evidence exists with regard to psychoeducation, family interventions, CBT, social skills training etc. [12].

The national guidelines on schizophrenia of the German Society for Psychiatry, Psychotherapy and Neurology (DGPPN) [1] recommend the application of various forms of psychotherapy.

Moreover, "creative therapies" like art therapy, music therapy, dance and drama therapies are broadly recommended without considering scientific evidence for the specific techniques.

Jones et al. emphasise in their 2010 Cochrane review [9] the general need of evidence from randomised controlled research regarding the psychotherapeutic treatment of schizophrenia. Of note, there is a striking lack of evidence on the efficacy of these approaches in patients experiencing acute episodes of the disorder and exhibiting a higher degree of thought disorder, difficulties to establish social contact or to express themselves verbally. In contrast, clinical experience suggests that the early use of psychotherapeutic interventions in this patient group might be of substantial benefit with respect to their ability to deal with the impact of symptoms and other illness-associated factors, to social interaction and to the mitigation of stigma. Here, creative therapies might be particularly efficient.

The putative advantages of art therapy are based on a number of theoretical assumptions:

Art therapy might have various modes of action, comprising the therapeutic relationship, the artistic process and the creator's relating to her/his work. From a psychodynamic point of view, art therapy can be considered a tripartite process, with the material/ artwork mediating the relationship between patient and therapist. As many patients in acute psychotic episodes are unable to directly establish social contact without being overwhelmed by fear, the non-verbal approach of art therapy and the mediating properties of the artwork allow for a subtile regulation of closeness and distance and a less frightening way of communication and self-expression. The interventions of the therapist are often experienced as less intrusive than in dyadic relationships, as they are mainly directed towards the creative process. They have a safe-guarding, encouraging and holding function in a situation of self-exporation. The physical qualities of the different materials may correspond to different inner reactions, feelings, memories and fantasies. Mental states may translate into visible and touchable forms, the reflection of which can help patients to regain orientation in their emotional world and foster self-reflection and emotional awareness. The experience of creativity and the production of coherently and objectively perceivable reality can furthermore strengthen self-esteem and prevent discouragement. Another important therapeutic ingredient is the group setting, allowing to take different perspectives, to jointly reflect and appreciate the pieces of art [2; 3; 10].

The current state of scientific evidence in art therapy in schizophrenia is reported by Ruddy et al. (2005) [4] in a systematic review. Only 2 out of 61 studies were RCTs conducted under sufficient methodological rigour. Green et al. (1987) [5] in their study of 47 outpatients with mixed diagnoses (50% participants with schizophrenia) investigated the effects of 10 sessions of art therapy every 2 weeks compared to patients receiving TAU. Patients receiving art therapy were reported to show improved social interaction and self-esteem and were more likely to complete the trial. Richardson et al. (2002) [6] compared 43 outpatients with chronic schizophrenia after a 12-week course of weekly art therapy with 47 patients treated as usual. Despite high drop-out rates the intervention group experienced a significantly greater reduction of negative symptoms at 6-months follow-up compared to controls. There was a trend for favourable effects of art therapy on social functioning, but not on quality of life and other symptom scales. A number of other studies were non-randomised or case-reports.

## Rationale

It can be concluded that preliminary evidence from outpatients with schizophrenia points to positive effects of art therapy regarding symptoms, self-esteem and social functioning. Art therapy represents a widely applied and clinically valuable form of psychotherapy for the treatment of mental disorders and in the rehabilitation of somatic disorders. However, there is only insufficient evidence for its efficacy and harmlessness regarding the treatment of patients with psychotic disorders from randomised controlled research.

# Trial Objectives and Purpose

This pilot randomised controlled trial will serve to generate preliminary data on the efficacy and safety of art therapy in patients in acute/ subacute episodes of schizophrenia. Results will allow to prepare a larger multi-centre RCT including the determination of sample-sizes.

**Primary objective** of the pilot study is to determine whether an adjunctive administration of art therapy in addition to TAU will lead to a more substantial symptom reduction in hospitalised patients with schizophrenia compared to standard treatment.

Primary endpoints are the Scale for the assesment of positive symptoms (SAPS) [17], the Scale for the assesment of negative symptoms (SANS) [18] and the Calgary depression rating scale for schizophrenia (CDSS) [19] as well as psychosocial outcome, measured by the Global assessment of functioning scale of the DSM-IV-TR.

**Secondary objectives** refer to the question, which other domains of experience and functioning may be impacted by art therapy. According to previous evidence and theoretical considerations about possible mechanisms of action of art therapy we chose the following constructs and

Secondary endpoints:

- General satisfaction with care (ZUF-8 [22; 23], a modification of the General Satisfaction Questionnaire [22]),
- Quality of life (Modular System for Quality of Life, MSQoL [11]),
- Self-efficacy/ locus of control (Questionnaire for competence and control: Fragebogen zu Kompetenz- und Kotrollüberzeugungen, FKK [20]),
- Mentalising capacity (1.: Reading Mind in the Eyes Test [29, 30]; 2.: Levels of emotional awareness scale, LEAS [34]),

**Exploratory analyses:**

- Qualitative and process-outcome analyses will be performed on an exploratory basis using footage of the art therapy sessions.

**The following data are documented as possible confounding variables:**

- Demographics (age, gender, education, genetic background, age and gender of siblings, marital status, housing, vocational status, assisted living/ community psychiatric care)
- Illness characteristics (year/ age of first manifestation, course of illness, number of episodes, number of psychiatric hospitalisations, course of antipsychotic treatment, non-pharmacological treatments, suicidality, familiy history
- Neurocognition (Multiple choice vocabulary test, MWT-B; Wisonsin card sorting test, WCST; Auditory verbal learning test, AVLT)

**Structured clinical interviews** for DSM-IV (SCID I and SCID II items referring to antisocial personality disorder) are performed to confirm inclusion and exclusion criteria with respect to diagnosis.

## Trial Design Overview

The study is planned and performed as a monocentric, randomised controlled pilot study with two parallel groups. The intervention group will be administered 12 sessions of psychodynamic art therapy (twice weekly over 6 weeks, 90 minutes per session), in groups of up to 5 patients, led by a trained art therapist experienced in the treatment of psychoses. The intervention will be aided and each sessions will be video-taped by a trained auxiliary person.

Patients randomisd to the control group will receive treatment as usual (TAU), including all indicated therapy options provided by the study centre. Allocation is open for patients, the art therapist, supervisors and all persons directly involved in the practical execution of the trial.

Psychopathological ratings (SAPS, SANS, CDSS, GAF) are performed by clinicians responsible for the study who are blind to randomisation status. In this pilot study, at least 15 patients will be included into each arm. The total individual trial duration is 12 weeks.

## Trial Duration/Timetable

The trial will be started on January 15, 2011 after a positive vote of the Institutional Review Board (Ethics committee of the Charité University Berlin). From this date, recruitment will take place and is expected to continue until June, 2011. Approximately 30 patients will be included.

The study will be finished after the follow-up phase of the last patient included. Data management and statistical analyses are planned for QIII/IV/2011, the final report for December, 2011.

# Participant Eligibility

## Inclusion Criteria

- Diagnosis of schizophrenia according to DSM-IV
- Age 18-64 years
- Sufficient German language competence
- Written informed consent (DvH, ICH-GCP)

## Exclusion Criteria

- Organic brain disorder
- Any other psychiatric disorder apart from schizophrenia according to DSM-IV- axis I
- Antisocial personality disorder asccording to DSM-IV
- Relevant somatic disorder imparing cerebral function
- Relevant abuse alcohol and illegal drugs (urine drug screen)
- Inability to understand and comply with the requirements of the study and to give written informed consent
- Inability to participate in a group psychotherapy setting:
  - massive agitation, hostility oder aggression
  - severe impulsiveness
  - severe paranoid ideation
- Current endangerment of others
- Current suicidal intent or massive tendency to self-harm
- Hospitalisation according to Berlin Mental Health Law (PsychKG)

## Rationale for inclusion of minors or other persons not able to give informed consent

Minors or patients being not able to give informed consent will not be included. In addition, legal representatives of patients will be informed about study participation.

# Investigational therapy

## Description of the art therapy / trial intervention

Art therapy will be administered in a group setting of up to 5 patients twice weekly. The twelve sessions of psychodynamic art therapy (twice weekly over 6 weeks, 90 minutes per session) are led by a trained art therapist experienced in the treatment of psychoses. The intervention will be aided and each sessions will be video-taped by a trained auxiliary person. Patients will chose freely the topic of their work and the materials they prefer, but may be supported in this process by the therapist encouraging patients to try out materials and techniques, by a choice of illustrated art books and postcards. The therapist may intervene only if the patient requires technical advice, needs encouragement or might become disappointed. At the end of each session materials will be put away, and the images will be presented to the group. Patients are free to decide whether they would like to comment on their work. In this phase, phenomenogical description is more important than interpretation. If the patient agrees, group members may also reflect on her/his image and reveal their own impressions and associations. The sessions are closed after the safe storage of the images in folders. The artworks are kept until the end of hospital treatment. At the time of discharge, patients take their folders home.

### Side effects and possible adverse events

The processing of anxiety, inner conflict or topics linked to paranoid ideation during therapeutic intervention could lead to a temporary destabilization of the patient with increasing dynamics of delusions, hallucinations and formal thought disorder or depression. Possible side effects/ complications would be exacerbation of psychotic symptoms, suicidal ideation, suicide attempts, suicide and aggression.

Adverse effects may also result from the treatment in a group setting. Hoffmann et al. therefore created a list of indications and contraindications for group psychotherapy (see also [24] and [25]). Participants should be able to adhere to the framework agreements (such as dates, duration). Psychotic symptoms of other patients might impose a burden on participants, and problems may arise from unfavourable group dynamics that might not always be resolved by the therapist. However, the specific technique of art therapy as well as the inpatient setting are suitable to recognise and minimise risks. Art therapy is less demanding with respect to the mental stability of patients compared to other group therapies, because it allows for a unique triadic interaction between patient, therapist and work of art. Art therapy offers a creative space that can bear protective properties. A lot of time is spent working silently, and adverse tendencies in group dynamics can be effectively controlled by the therapist. However, individual adverse reactions to the group setting or as a result of high emotional intensities evoked by self-exploration in the creative process can not be completely excluded.

### Treatment schedule

Patients are treated in groups of up to five people. In the pilot study twelve sessions of art therapy will be performed, offered twice weekly. A session lasts 90 minutes.

### Treatment compliance

In this pilot study, only inpatients will be included. Patients receive a reminder card with the dates of all 12 sessions and the necessary study examinations. The majority of art therapy sessions will take place in the context of inpatient treatment, but the last remaining sessions can be attended after discharge. Of note, study participation must not interfere with hospital discharge plans. Patients will be reminded and motivated to participate in every session. After discharge, patients might be reminded by telephone calls to participate in the art therapy sessions and follow-up examinations. Compliance is ensured by continuous documentation of session attendance.

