## Blinding Procedures

Blinding
Participants, art therapists and supervisors as well as clinical staff involved in the administration of art therapy and practical organisation of the study are aware of allocation status. Clinical ratings are performed by psychiatrists responsible for the study, but not involved in the direct treatment of the participating patients and blind to randomisation. Patients are instructed not to inform the assessor of their allocation status.

Methods of Unblinding and Discontinuation

Unblinding of the psychiatrists responsible for clinical study assessments is only allowed for safety reasons. Regular unblinding of the trial is planned at the end of the trial (last visit, last patient), after closing the database.

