## Assessment of causality

The determination of the likelihood that the study intervention caused the AE (causality assessment) will be provided by the investigator. The assessment of causality will be determined by the investigator and recorded on the CRF AE page and SAE form according to the investigator’s best clinical judgment. The following questions should be considered in determining the relationship between the study intervention and the AE:

- Was the study intervention administered?
- Was there another obvious cause of the AE?
- What was the temporal sequence of the onset of the AE relative to the study intervention?
- Was the AE consistent with the known pattern of response to study intervention?
- Could the subject‘s clinical state, environmental or toxic factors, or other modes of therapy administered to the subject have caused or modified the AE?
- Did the AE resolve or improve after study intervention was discontinued or reduced?
- Did the AE remain the same or worsen after study intervention was discontinued or reduced?
- If the subject was re-exposed (rechallenged), did the AE recur or worsen upon re-exposure? Did the AE not recur or improve with re-exposure? (Clinical judgment should be used for determining if rechallenge is appropriate.)

Taking into account any of the above factors, the Investigator will assess the causality of the individual AEs using one of the following:

| **unassessable:** | Due to insufficient information the causality cannot be assessed. |
| --- | --- |
| **unlikely:** | The adverse event may easily be explained with sufficient other information that there is no causality with the study intervention. |
| **possible:** | The adverse event follows a reasonable temporal sequence after administration of the intervention or a known response pattern to the suspected intervention. It could readily have been produced by the patient´s clinical state, environmental or toxic factors, or other modes of therapy administered to the patient. |
| **probable:** | The adverse event follows a reasonable temporal sequence after administration of the intervention or a known response pattern to the suspected intervention. It could not be reasonably explained by the known characteristics of the patient´s clinical state, environmental or toxic factors, or other modes of therapy administered to the patient. It disappears or decreases on cessation or reduction in dose of study intervention. |

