# Documentation

## Case Report Forms (CRF)

All assessed data will be documented in paper CRF.

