## Data Collection / Case Report Forms

Data will by collected via paper-CRF forms (CRF). CRFs will be stored separately from the patients' identification log. CRFs will be filled in by ball-pen, pencils are not allowed. Corrections can be made by crossing out an entry, correct onformation is given directly next to the previous entry, the study responsible/physician will sign the correction with his name, date and reason for correction. Data fields left open due to missing information have to be commented on.

The CRFs will be archived for 10 years.

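### The patient's reminder card combines art-therapy session dates with rating-visit dates, so a card brought to Visit 2 or 3 could show the blinded rater the arm

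*Protocol*

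**What the plan says.** On the card, Protocol 5.1.3 (Treatment compliance): "Patients receive a reminder card with the dates of all 12 sessions and the necessary study examinations". The same section allows the last sessions to be attended after discharge and foresees telephone reminders for sessions and follow-up examinations. It adds: "Compliance is ensured by continuous documentation of session attendance". It does not say where attendance is recorded.

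On the raters, Protocol 5.5 (Blinding Procedures): "Clinical ratings are performed by psychiatrists responsible for the study, but not involved in the direct treatment of the participating patients and blind to randomisation". For the contact between patient and rater it adds: "Patients are instructed not to inform the assessor of their allocation status". It also limits deliberate unblinding: "Unblinding of the psychiatrists responsible for clinical study assessments is only allowed for safety reasons".

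On the forms, Protocol 10.1: "All assessed data will be documented in paper CRF". Section 9.5 has the investigator judge whether an adverse event was caused by the intervention, and this is "recorded on the CRF AE page and SAE form according to the investigator’s best clinical judgment". The only separation of forms that is described is in 12.1: "CRFs will be stored separately from the patients' identification log".

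**The concern.** All four primary endpoints (SAPS, SANS, CDSS and GAF; section 3) are clinician ratings. Patients, therapists, supervisors and the staff who organise the study know the allocation, so the blinded rater is the main protection of these endpoints against expectation. The trial itself gives patients a paper that shows the arm and also serves as the appointment reminder for the blinded ratings. If raters learn the arm in this way, a difference in ratings may partly reflect what they expect of art therapy. Section 13.1 says the pilot is run to estimate effect sizes for a larger trial, so such an error would carry over into the planning of that trial.

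**Working it through.** The protocol gives no figure to reproduce here. The check sets its statements side by side.

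1. **Does the card identify the arm?** It carries the dates of 12 sessions (5.1.3). The control arm receives standard treatment (5.2), and additional art therapy is not allowed in either arm during the trial (5.3). Session dates therefore fit only an art-therapy patient. The protocol does not say what card, if any, a control patient receives. If controls receive a card without sessions, that card would identify them too.

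2. **Which ratings are exposed?** Under 6.5 and the flow chart, the baseline examination comes before randomisation, so the card cannot affect it on that order. (The synopsis lists the two steps in the other order; I follow the main text.) Table 1 in 6.6 schedules SANS/SAPS, CDSS and GAF again at Visit 2, within 7 days after the intervention ends, and at Visit 3, around week 12. These are the exposed ratings, and they are the measurement points for the primary analysis in 13.2.3.

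3. **Is it plausible that the card comes along?** The patient holds it and it lists the examination dates. Discharged patients have to return for the remaining sessions and for the visits. That makes bringing the card foreseeable. The protocol does not say that patients bring it or that raters ask for it.

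4. **What stands in the way?** Raters do not treat the participants, may be unblinded only for safety reasons, and patients are told not to inform the assessor. Of these, only the last governs what happens between patient and rater at the visit, and it does not mention papers that the patient carries.

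5. **Is there a second route through the forms?** Answering the causality questions in 9.5 requires knowing whether the intervention was given. The raters are psychiatrists responsible for the study (5.5), and causality is judged by the investigator (9.5). The protocol does not say that these are different people, nor that the adverse-event pages are kept apart from the rating pages. Adverse events are asked about at every visit according to the synopsis, so contact between the rater and those pages is possible. It is not stated.

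6. **Size.** If a share q of ratings in the art-therapy arm is unblinded and each is scored s standard deviations more favourably, with control ratings unaffected, the bias in the arm difference is q × s. The documents give neither q nor s, so no figure follows from them.

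**The case against.** The strongest reply is that the blind is already protected. Raters are kept out of treatment, and an instruction not to inform the assessor can fairly be read to include not showing a session card. This has weight: the protocol does not ignore the risk, and no breach is shown. But the instruction leaves it to acutely ill patients to recognise that an appointment card discloses the arm, when the card could simply not carry that information.

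Three stronger readings are tempting, and the documents do not support them.

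- **That the rater's own paperwork shows the arm.** The card belongs to the patient. Section 10.1 names the medium, paper, and does not describe one undivided booklet that passes through the rater's hands. Sections 9.5, 9.6 and 12.1 speak of pages and forms in the plural. Attendance is not said to be in the CRF.
- **That the adverse-event page reveals the arm generally.** Adverse events are recorded for the whole trial, and causality entries such as unlikely or unassessable could occur in either arm. The page would be telling only in some cases, and the layout of the CRF is not shown.
- **That the bias has a known size.** Assuming q = 0.2 and s = 0.3 gives 0.2 × 0.3 = 0.06 SD; assuming q = 0.6 and s = 0.5 gives 0.6 × 0.5 = 0.30 SD. With 15 per arm, the standard error of a simple difference in means is √(2/15) = 0.365 SD. The first two figures are only products of chosen inputs. They show what would have to be known and are not evidence of bias. Nor is exposure confined to one arm with certainty, as step 1 of the check shows.

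**Conclusion.** The point holds as a weakness in a stated procedure. One patient-held card combines information that identifies the arm with the dates of the blinded ratings, and the protocol does not keep that card away from the rater. The rater could therefore learn the arm at Visit 2 or 3, for all four primary endpoints. This rests on one assumption outside the text: that some patients bring the card and it is seen. How often that would happen, and how far it would shift ratings, cannot be derived from the documents. The direction would depend on what raters expect of art therapy. The route through the CRF is weaker, because the protocol leaves rater access to the adverse-event pages open and does not affirm it; it justifies a precaution only. The case for acting is that the change costs almost nothing.

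**What to change.** - **Section 5.1.3:** issue two cards, both kept by the patient. The visit card is identical in both arms and lists only the study examinations. The session card goes to art-therapy patients and lists the 12 sessions. It must stay with the patient, or it no longer serves as a reminder.
- **Section 5.5:** tell patients to bring only the visit card to rating visits, in addition to the existing instruction.
- **Sections 9.5 and 10.1, as a secondary precaution:** record SAPS, SANS, CDSS and GAF on forms separate from the adverse-event and causality pages.

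The cost is one additional printed card and a minor change to the form layout, for about 30 patients. Treatment, visits and the analysis stay as they are.
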